### Randomization

Patients are randomly assigned to either RTX plus MMF, or RTX plus placebo group at an approximate ratio of 1:1 using the following allocation adjustment factors; medical institution, age, treatment history (presence or absence of immunosuppressive drug administration at the relapse immediately prior to enrollment, presence or absence of steroid administration at the relapse immediately prior to enrollment), interval between the last 3 relapses, presence or absence of history of SRNS.

Patients, their guardians, treating physicians, and individuals assessing outcomes and analyzing data are blinded to the patients’ assigned treatment. Apart from the data-monitoring committee, all treating physicians and other investigators remain blinded to the trial results until follow-ups are completed.

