### Statistical analyses

The primary aim of this study is to examine the superiority of RTX plus MMF combination therapy compared with RTX monotherapy in extending the duration to treatment failure. Based on a previous study, we hypothesize a 1-year event rate of 40% in the RTX treatment group and expect the RTX plus MMF treatment to decrease that to 20%. The planned sample size is 80 patients: 37 patients in each group will be needed to have 80% power for a log-rank test with a 5% significance level, under an assumption of proportional hazard rates, 3 years accrual, and one-and-a-half years follow-up. To allow for withdrawal of consent after participation in the study or loss to follow-up, we set the study size to 80 participants in total. The power calculation was performed using SAS version 9.3 (SAS Institute Inc., Cary, NC, USA). As a primary analysis, time-to-treatment failure is summarized using the Kaplan-Meier method and results compared using the log-rank test. The hazard ratios with 95% confidence intervals are estimated using Cox proportional hazard model. Secondary endpoints including time to relapse, time to FRNS, time to SDNS, time to SRNS, and B cell depletion period will be analyzed in the same manner as the primary endpoint. Model based analysis will be performed as needed. Relapse rate will be compared by permutation testing. Total steroid dose will be compared with the Wilcoxon test.

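### The primary log-rank test and Cox model, as stated, leave out the factors used to balance allocation; adjusting for the patient-level ones would add power if they predict failure

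*Protocol article*

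**What the plan says.** The Randomization section of the protocol article assigns patients about 1:1, "using the following allocation adjustment factors; medical institution, age, treatment history". Treatment history there means two items: immunosuppressant use and steroid use at the relapse before enrolment. The list ends with the interval between the last three relapses and history of steroid-resistant disease. That is five factors as listed, or six if treatment history counts as two. Institution is one of them; the other five items belong to the patient.

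The Statistical analyses section names a Kaplan-Meier summary and the log-rank test as the primary analysis of time to treatment failure, and adds: "The hazard ratios with 95% confidence intervals are estimated using Cox proportional hazard model". It mentions no stratum and no covariate for either. A later sentence allows model-based analysis where needed, but it follows the secondary endpoints, names no covariate and is not tied to the primary comparison.

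The sample size is stated for an ordinary log-rank test: "37 patients in each group will be needed to have 80% power".

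**The concern.** When allocation is balanced on factors that predict the outcome, the treatment difference varies less between trials than under simple randomisation. A log-rank test that leaves those factors out does not credit this. It can then reject less often than its nominal level under the null, and it loses power against an analysis that includes the factors.

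The article never calls the factors prognostic, but its text makes a link plausible. The Background says that stopping cyclosporine often brings frequent relapses back, and calcineurin inhibitors are tapered from day 86 to about day 169, inside the observation period. The endpoint is built from relapse frequency and relapse on or soon after steroids, which is the history that the relapse-interval and steroid-use factors record. At stake is efficiency in a trial of 80 patients, from data already collected for allocation.

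**Working it through.** **1. The plan's own figure.** Inputs, all from Statistical analyses: "we hypothesize a 1-year event rate of 40% in the RTX treatment group", 20% with MMF, "3 years accrual, and one-and-a-half years follow-up", and "80% power for a log-rank test with a 5% significance level". The test is taken as two-sided, because one-sided calculation does not reproduce the stated size.

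- Exponential hazards: −ln(0.6) = 0.511 and −ln(0.8) = 0.223 per year, so HR = 0.223/0.511 = 0.437.
- Events (Schoenfeld): 4 × (1.960 + 0.842)² / (ln 0.437)² = 46.
- Event probability with uniform 3-year accrual and 1.5 years minimum follow-up, 1 − [exp(−1.5λ) − exp(−4.5λ)]/(3λ): 0.762 (control) and 0.478 (MMF).
- Expected events with 37 per arm: 37 × (0.762 + 0.478) = 45.9, power 80.1%. A Lakatos-type calculation gives 79.4%.

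The stated size therefore reproduces for an ordinary log-rank test (38 per arm by Schoenfeld after rounding up), with no credit taken for adjustment. At 80 patients the same assumptions give 82% to 83%.

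**2. Events if observation ends at day 505.** The Observation period section runs from day 1 to day 505, that is 504/365.25 = 1.38 years. Event probabilities are 1 − exp(−0.511 × 1.38) = 0.506 and 1 − exp(−0.223 × 1.38) = 0.265. With 40 per arm this gives 40 × (0.506 + 0.265) = 30.8 events and power of 61% (Lakatos-type) to 63% (Schoenfeld), before any question of adjustment.

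**3. Effect of adjustment, by simulation.** Setting: 80 patients, all censored at day 505; marginal 1-year rates held at the plan's 40% and 20%; 1,500 trials per row. Assumed, because the article does not give them: biased-coin minimisation (probability 0.8) over 27 institutions and five binary patient factors, and the same hazard ratio for each of the five. Monte Carlo standard error is about 1.3 points for power and 0.6 points for type I error.

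| HR per factor | Power, unadjusted log-rank | Power, Cox with 5 factors | Difference | Power, log-rank on 2 strata factors | Type I, unadjusted | Type I, Cox |
|---|---|---|---|---|---|---|
| 1.0 | 60.9% | 61.3% | 0.4 | 59.5% | 4.6% | 5.5% |
| 1.3 | 60.3% | 62.6% | 2.3 | 58.9% | 4.9% | 6.3% |
| 1.5 | 62.7% | 66.9% | 4.2 | 62.5% | 4.6% | 6.1% |
| 2.0 | 60.4% | 71.4% | 11.0 | 63.1% | 2.6% | 6.0% |
| 2.5 | 59.7% | 75.3% | 15.6 | 63.0% | 3.0% | 5.8% |

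A repeat simulation of the same setting gave 62% against 62% (HR 1.0), 61% against 66% (1.5) and 60% against 72% (2.0). The unadjusted type I error was 2.7% at HR 2.0, and the Cox test's size was 5% to 7%.

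**4. What does not work.** A log-rank test stratified by every factor including institution has power of 0.3% to 1.8%: 80/27 is about 3 patients per site, so almost no stratum is informative. Stratifying on only two binary factors recovers little (59% to 63%, against 60% to 63% unadjusted).

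**5. Cost in parameters.** Treatment plus five covariates is six parameters, so 30.8/6 is about 5 events per parameter. This fits with the slightly liberal size of the adjusted Wald test, which also accounts for part of the power difference in the table.

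**The case against.** The strongest objection is that the article is silent on strata and covariates rather than excluding them. Such detail often sits in a statistical analysis plan, which is not shown here, so a reader should not infer that the trial has decided to ignore the factors. That stands as a limit on the point: if a separate plan already specifies adjustment, confirming it is enough. It does not remove the point, because the article does name its primary test and estimator, and adjustment would change that stated method.

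Three stronger readings are tempting, and the documents do not support them.

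- **That the test is invalid or certainly conservative.** It is valid, and any error is on the cautious side. No effect size is given for any factor, and at a hazard ratio of 1.0 to 1.5 the type I error is 4.6% to 4.9%, indistinguishable from 5%. Visible conservatism needs 2.0 or more on all five factors at once.
- **That the unadjusted hazard ratio is biased toward 1.** Unadjusted and covariate-adjusted hazard ratios are different estimands. The 40% and 20% are population event rates, so 0.437 is a marginal ratio. In the simulation the conditional ratio that yields those same rates moves from 0.437 to 0.368 as the factors strengthen, with no error in either quantity.
- **That missing adjustment explains the low power.** The unadjusted test has 60% to 63% power at every factor strength. That level comes from ending observation at day 505, against the 3 + 1.5 years in the sample-size calculation. It applies only if later failures do not count; Table 1 also lists relapse evaluation at 36/48 months.

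**Conclusion.** The point holds as a conditional loss of efficiency, worth fixing but not an error in the plan. The stated primary analysis uses none of the allocation factors. With 80 patients observed to day 505, the power forgone is about 0 to 5 points if each patient-level factor carries a hazard ratio of 1.0 to 1.5, and 11 to 16 points at 2.0 to 2.5, where the unadjusted type I error falls to about 3%. These figures rest on assumed factor strengths, an assumed minimisation scheme and five binary factors. They also compare tests of slightly different size, so the gain at exactly 5% would be somewhat smaller. Direction is more secure than size. The stated 80% power does not depend on adjustment.

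**What to change.** Before allocation codes are released for analysis, prespecify the treatment comparison and hazard ratio from a Cox model adjusted for the patient-level allocation factors: age, immunosuppressant use and steroid use at the last relapse, the interval between the last three relapses, and history of steroid resistance. Leave institution out, and say why. Report the unadjusted log-rank test and hazard ratio alongside, and state that the adjusted hazard ratio is conditional on the covariates.

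Because the adjusted test ran at about 5% to 7% with about 31 events, either limit the covariates to a prespecified few or take the p-value from re-randomisation under the trial's own allocation algorithm. If a separate analysis plan already settles this, a sentence confirming it is enough.

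The cost is wording, plus programming if re-randomisation is used; the factors are already recorded. The follow-up assumption behind the sample size needs to be addressed separately, since adjustment does not resolve it.

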## Live vaccines

### The discontinuation of investigational drug administration

Investigators are to discontinue the administration of investigational drugs to participants to whom any of the following circumstances apply:If treatment failure (FRNS, SDNS, or SRNS) is observed during the observation period.If prohibited drug 1.2. (see above) is used as a treatment for nephrotic syndrome.If the participant or legal representative requests discontinuation of the administration of the investigational drug.If the investigators determine the continuation of investigational drug administration to be difficult for any other reason such as the occurrence of adverse events.If the participant becomes pregnant.

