### Allocation key opening

To maintain blinding, the “allocation codes” will be disclosed after the entire clinical trial is completed and all data and determination secured. However, if any of the following circumstances apply, the allocation code of the patient will be urgently disclosed.The participant experiences a serious adverse event that leads to death or is life-threatening.The participant experiences another serious adverse event and it is determined the information is essential in considering the relevant patient’s treatment.There is determined to be treatment failure (FRNS, SDNS or SRNS).The participant becomes pregnant and discontinues the administration of investigational drug.

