### Outcomes

The primary endpoint is defined as the time-to-treatment failure (development of frequent relapses, steroid dependence or steroid resistance). Diagnosis of FRNS, SDNS, and SRNS is based on relapse dates according to the ISKDC (Table 2). The secondary end points are time to relapse, relapse rate, time to FRNS, time to SDNS, time to SRNS, total steroid dose, peripheral blood B cell depletion period and adverse events. Adverse events are recorded throughout the trial period and assessed using CTCAE.

**Table 2 Tab2:** Definitions [6]

A. *Nephrotic syndrome*	The presence of a urine protein-to-creatinine ratio of 1.8 or above and serum albumin of 2.5 g/dL or below.
B. *Complicated nephrotic syndrome*	A patient that fulfills any of the following criteria is deemed to suffer from complicated nephrotic syndrome: (1) Diagnosed with frequent relapse or steroid dependence and once again diagnosed with frequent relapse or steroid dependence after completion of immunosuppressive drug therapy (cyclosporine, cyclophosphamide, mizoribine, etc.) (2) Diagnosed with frequent relapse or steroid dependence and once again diagnosed with frequent relapse or steroid dependence during immunosuppressive drug therapy (cyclosporine, cyclophosphamide, mizoribine, etc.) (3) Diagnosed with steroid resistance and diagnosed with frequent relapse or steroid dependence during or after the completion of immunosuppressive drug therapy (cyclosporine or combination of cyclosporine and methylprednisolone, etc.)
C. *Remission*	Negative protein on urine dipstick in the first morning urine for 3 consecutive days.
D. *Steroid sensitivity*	When the daily administration of prednisolone at 60 mg/m^2^/day leads to remission within 4 weeks.
E. *Relapse*	Protein 2+ or above detected by urine dipstick in the first morning urine for 3 consecutive days and prednisolone treatment is required.
F. *Frequent relapse*	Two or more relapses within 6 months after initial remission or 4 or more relapses within any 12-month period.
G. *Steroid dependence*	Two consecutive relapses during the reduction of steroid therapy or within 2 weeks of discontinuation of steroid therapy.
H. *Steroid resistance*	When the daily administration of prednisolone at 60 mg/m^2^/day does not lead to remission within 4 weeks.

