## Discussion

The purpose of this trial is to examine its safety and assess whether RTX plus MMF combination therapy is superior to RTX plus placebo for the maintenance of remission after RTX treatment in children with complicated FRNS/SDNS. Recently, RTX dramatically altered the treatment of complicated FRNS/SDNS [34]. Some patients can attain a ‘steroid-free period’ and/or ‘cyclosporine-free period’, while some cases tend to relapse after the recovery of B cell counts [14–16]. However, MMF has recently been focused on as a new treatment for childhood-onset nephrotic syndrome [21–30]. MMF is an immunosuppressive agent whose mechanism is similar to mizoribine in its inhibitory effect on the de novo pathway of nucleic acid synthesis [35]. In addition, we previously found that SDNS patients who do not relapse after RTX treatment were taking MMF [14]. Therefore, upon receiving the results of a pilot study, [31] we initiated a multicenter, double-blind, randomized, placebo-controlled trial to assess the efficacy and safety of MMF after RTX therapy in children with complicated FRNS/SDNS.

At present, there is a consensus that after RTX treatment, we do not use immunosuppressants until patients lapse into FRNS/SDNS again. Although the efficacy of MMF was shown in the pilot study, MMF is not an established treatment for maintenance therapy after RTX. Thus, it is reasonable to set the control group as immunosuppressant free. Simultaneously, we must pay careful attention so as not to restrict the chance for appropriate treatment in participants. To rescue the patients who fall into treatment failure, we are setting an urgent key open system. If a patient falls into FRNS, SDNS, or SRNS, the allocation code will be opened immediately and treatment conducted using immunosuppressants as soon as possible.

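### Kaplan-Meier curves for time to FRNS, SDNS and SRNS do not carry over cleanly from the composite: if follow-up is cut at another failure type, component risk is overstated, more so in the control arm

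*Protocol article*

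**What the plan says.** The primary endpoint (Outcomes) is "time-to-treatment failure (development of frequent relapses, steroid dependence or steroid resistance", so the first of the three is the event. Under Statistical analyses, "time-to-treatment failure is summarized using the Kaplan-Meier method and results compared using the log-rank test", with hazard ratios from a Cox model. The same section extends this to the components: "time to FRNS, time to SDNS, time to SRNS, and B cell depletion period will be analyzed in the same manner" as the primary endpoint. It adds that model-based analysis will be done as needed, which does not replace the stated method.

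Three other places describe what the first component event sets off:

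- The section on discontinuing the investigational drug lists as a reason to stop: "If treatment failure (FRNS, SDNS, or SRNS) is observed during the observation period".
- Allocation key opening lists as a reason for urgent disclosure: "There is determined to be treatment failure (FRNS, SDNS or SRNS".
- The Discussion says that on FRNS, SDNS or SRNS "the allocation code will be opened immediately and treatment conducted using immunosuppressants as soon as possible". The section on concomitant drugs lifts the ban on immunosuppressants once treatment failure is determined.

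The article does not say whether a patient stays at risk for the other two components after the first failure. Table 1 schedules relapse evaluation at drug discontinuation and again in the follow-up column (36/48 months), while the observation period is defined as ending on day 505.

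**The concern.** Kaplan-Meier suits the composite, because nothing that happens after the first failure matters to it. For a single component, a first failure of another type changes treatment and blinding before the component has occurred. The Table 2 definitions show how. A patient can meet SDNS at a second relapse. If the early FRNS route (two relapses within 6 months after initial remission) does not apply, FRNS needs four relapses in 12 months. By then the patient is off study drug, unblinded and on rescue, so FRNS on assigned treatment can no longer be observed.

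That leaves two ways to draw the curve. One censors the patient at the other failure and so treats a patient who has already failed as still able to fail on study drug. The other follows the patient through, and the curve then describes randomised treatment up to the first failure and unblinded rescue after it. At stake are the component risks shown for three secondary endpoints and any arm difference a reader takes from those curves.

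**Working it through.** **Check that the planning inputs are understood.** The article states "we hypothesize a 1-year event rate of 40% in the RTX treatment group and expect the RTX plus MMF treatment to decrease that to 20" (per cent), and "37 patients in each group will be needed to have 80% power for a log-rank test with a 5% significance level", with 3 years of accrual and 1.5 years of follow-up.

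- Constant hazards: control L = -ln(0.6) = 0.511 per year; MMF L = -ln(0.8) = 0.223 per year; hazard ratio 0.437.
- Schoenfeld, two-sided 5% (an assumption, since sidedness is not stated), 80% power: about 46 events.
- Event probabilities with uniform 3-year accrual plus 1.5 years: 0.762 and 0.478.
- Patients per arm: 45.8 / (0.762 + 0.478) = 36.9, so 37. The stated figure reproduces, and these hazards can be used below.

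**Component risk if patients are censored at another failure type.** Let s be the share of first failures that meet the component. This is an assumption, because the article gives no shares; it is varied below and taken as equal in both arms. Let t = 505/365.25 = 1.383 years.

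- One minus Kaplan-Meier = 1 - exp(-s × L × t)
- Cumulative incidence = s × (1 - exp(-L × t))

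L × t is 0.706 in control and 0.309 with MMF, so any-failure risk at day 505 is 50.7% and 26.5%.

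| s | Control: 1-KM | Control: cum. inc. | Ratio | MMF: 1-KM | MMF: cum. inc. | Ratio |
|---|---|---|---|---|---|---|
| 5% | 3.5% | 2.5% | 1.37 | 1.5% | 1.3% | 1.15 |
| 10% | 6.8% | 5.1% | 1.35 | 3.0% | 2.7% | 1.14 |
| 40% | 24.6% | 20.3% | 1.21 | 11.6% | 10.6% | 1.09 |
| 50% | 29.8% | 25.3% | 1.17 | 14.3% | 13.3% | 1.08 |
| 70% | 39.0% | 35.5% | 1.10 | 19.4% | 18.6% | 1.05 |
| 90% | 47.0% | 45.6% | 1.03 | 24.3% | 23.9% | 1.02 |

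Ratios are from unrounded values. At s = 50% the difference between arms reads 29.8 - 14.3 = 15.5 points by Kaplan-Meier against 25.3 - 13.3 = 12.0 points by cumulative incidence. The overstatement is larger in control because more patients there fail in some other way first.

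**Component risk if patients are followed through.** No formula applies, because the article gives no event rates under rescue. The overstatement above does not arise. Relative to the risk on assigned treatment, the bias can go either way.

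**The case against.** The strongest reply is that the article states no censoring rule for the components. Such rules are commonly left to the full protocol or the analysis plan, and Table 1 allows for evaluation after drug is stopped. This stands in part: a flat statement that the component curves will be overstated is not supported, because it holds only under censoring. What the article does fix is the method, and that method needs a change or a label on either reading. Following patients through is a legitimate treatment-policy estimate, provided it is presented as one.

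Second, the three components are not competing events in the strict sense. Table 2 makes none of them exclude another, and FRNS and SDNS are built from the same relapse dates, so one relapse can complete both. The on-study relapse course tapers prednisolone over three 2-week steps. A steroid-dependent relapse therefore falls within roughly 8 weeks of remission, and many such patients may also meet the 6-month FRNS limb, depending on how initial remission is read. This stands, and it shrinks the effect, as the 90% row shows. It also means that component risks adding up to more than the composite risk is not by itself evidence of error, though a reader might infer that.

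Third, the log-rank test and Cox hazard ratio remain valid under censoring as cause-specific comparisons, and the article plans no absolute risk difference per component. This stands too: the fault lies in the risk curves. The inflated difference arises only when someone reads it off them.

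A reader might also carry the calculation to several years, where the gap widens. The article ends the observation period at day 505 and the Discussion gives 18 months, so a longer horizon is not used here.

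**Conclusion.** The point holds in conditional form. The stated method fits the composite but does not carry over cleanly to its components, because the first failure changes treatment and blinding. If component follow-up is cut at another failure type, one minus Kaplan-Meier overstates component risk at day 505 by a factor of about 1.10 to 1.37 in control and 1.05 to 1.15 with MMF for shares of 5% to 70%. In control the factor is about 1.03 at a 90% share. These figures rest on constant hazards at the planning rates, equal shares in both arms and shares that the article does not supply. If follow-up continues, there is no such overstatement, but the curve includes rescue and unblinding.

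Only the three component secondary endpoints are touched. The primary endpoint, its test and the sample size are unaffected, and the component log-rank and Cox results stand as cause-specific comparisons.

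**What to change.** In the analysis plan:

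1. State for each component whether follow-up ends at the first failure of any type.
2. Report the Aalen-Johansen cumulative incidence of each component at first failure. Count a patient who meets FRNS and SDNS at the same relapse as having both. Treat a first failure that does not meet the component as the competing event.
3. Keep the log-rank test and Cox model, labelled as cause-specific comparisons.
4. Show component events after the code break separately, as descriptive or treatment-policy results that include rescue and unblinded follow-up.

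The cost is some wording, a standard procedure and slightly more output, with no new data. Reported component risks will be lower than under censored Kaplan-Meier.
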